### Plans to promote participant retention and complete follow-up {18b}

Follow-up visits (at weeks 18 and 24) will be scheduled by phone or WeChat. When the patients complete the follow-up, the transportation subsidy will be paid to promote participant retention and complete follow-up.

### Data management {19}

After the study is completed, the CRFs generated by each trial center will be submitted to the responsible unit of the study (Shanghai Municipal Hospital of TCM). Data entry will be performed separately by two independent research assistants and cross-checked to ensure the accuracy of the data. After data entry, the first unblinding will be performed, and the data will be divided into two groups based on the intervention. After ensuring that the details of the intervention are not displayed, the data will be given to the Statistical Center of Shanghai University of TCM for statistical analysis. When the statistical analysis is completed, the second unblinding will be performed, and the data will be locked. Only the senior supervisor will be authorized to open the data.

### Confidentiality {27}

Records generated during the study (e.g., informed consent and CRFs) will be kept in the responsible unit and locked at the end of the study, with only the senior supervisor having access to these files. The information will be used for this study only and will not be used for any other purpose.

### Plans for collection, laboratory evaluation, and storage of biological specimens for genetic or molecular analysis in this trial/future use {33}

N/A. No biological specimens will be involved in this study.

## Statistical methods

### Statistical methods for primary and secondary outcomes {20a}

SPSS V26 (IBM Corp., Armonk, NY, USA) will be used for both data input and analysis. Statistical analysis will be performed as follows. First, descriptive statistics will be used for all outcome measures at each measurement point to summarize the results. For normally and nonnormally distributed measurement data, the mean ± standard deviation, and median, will be used for the statistical description of the degree of trend, and dispersion, respectively. Second, differences in the mean change in primary and secondary outcomes from baseline to each time point between the groups will be compared using two independent samples *t*-tests or the Mann–Whitney *U*-test. Finally, chi-square tests will be used for blind evaluation. Statistical significance will be set at a *p*-value < 0.05 (two-sided). Table 3 summarizes the statistical analysis of primary and secondary outcomes.

**Table 3 Tab3:** Variables, measures, and methods for statistical analysis of primary and secondary outcomes

Variable/outcome	Outcome measure	Methods of analysis
1) Primary		
The mean of change in shoulder function from baseline to 4, 12, 18, and 24 weeks	Constant-Murley score (continuous)	*T*-test or Mann–Whitney *U*-test^a^
2) Secondary		
The mean of change in shoulder pain from baseline to 4, 12, 18, and 24 weeks	Visual analogue scale (continuous)	*T*-test or Mann–Whitney *U*-test^a^
The mean of change in shoulder range of motion from baseline to 4, 12, 18, and 24 weeks	Active range of movement of shoulder joint (continuous)	*T*-test or Mann–Whitney *U*-test^a^
The mean of change in quality of life from baseline to 4, 12, 18, and 24 weeks	The 36-Item Short Form Survey (continuous)	*T*-test or Mann–Whitney *U*-test^a^

^a^For data conforming to normal distribution, *T*-test is used, and for data not conforming to normal distribution, Mann–Whitney *U*-test test is used

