#### Outcomes {12}

Primary and secondary outcomes are presented in Table 1.

**Table 1 Tab1:** Primary and secondary outcomes

	Primary outcome	Secondary outcomes		
Outcome measure	Shoulder function	Shoulder pain	Shoulder range of motion	Quality of life
Method of measurement	Constant-Murley Score [16]	Visual analog scale [17]	Active range of movement of shoulder joint [18]	The 36-Item Short Form Survey [19]
Analysis metric and method of aggregation	Difference in the mean of change from baseline between the two groups			
Time point	4, 12, 18, and 24 weeks. The principal analysis will be performed at 4 and 12 weeks	4, 12, 18, and 24 weeks		

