### Sample size {14}

The sample size is calculated based on our preliminary study, which was completed from November 2021 to February 2022. The prior research compared CMS changes from baseline to the end of 4-week treatment in patients receiving FSM or SM plus home-based exercise. Our previous results showed that CMS increased by 24.32 (μ_r_) in the FSM group and increased by 10.31 (μ_c_) in the SM group, and the standard deviation of the FSM group was 17.84 (*σ*). On the basis of the above data, when 1/3 of the standard deviation of the FSM group is selected for Δ, *α* = 0.025 (single-sided), *Z*_1−0.025_ = 1.96, 1 – *β* = 0.90, *Z*_1−0.10_ = 1.282, and the ratio of the number of subjects between the FSM group and SM group (*K*) = 1, using the following formula, 104 participants are required for each group: $${n}_{c}=\frac{{{\left({Z}_{1-\alpha }+{Z}_{1-\beta }\right)}^{2}\sigma }^{2}\left(1+\frac{1}{K}\right)}{{\left({\mu }_{r}-{\mu }_{c}-\Delta \right)}^{2}}$$$${n}_{r}={Kn }\ _{c}$$

On this basis, considering an estimated dropout rate of 20%, 125 cases will be needed for each group. Additionally, because there are three trial centers in this study, 15 additional cases are required for each group owing to the multicenter design. Therefore, a total of 280 participants will be enrolled in this study, with 140 participants in both the FSM group and the SM group.

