## Assignment of interventions: allocation

### Sequence generation {16a}

Eligible participants will be randomly assigned at a 1:1 ratio to either the FSM group or the SM group. The randomization scheme and allocation sequence will be generated via SAS PROC PLAN software (SAS Inc., Cary, NC, USA) by the Shanghai Medical Clinical Research Center (an independent third-party institution). The randomization list will be stratified by study center and will comprise the code, randomization number, and treatment regimen.

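### The unadjusted tests on change scores ignore baseline and center, and the normality switch can replace the mean difference with a different question

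*Protocol article*

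**What the plan says.** The protocol article, Statistical methods for primary and secondary outcomes {20a}, states that "differences in the mean change in primary and secondary outcomes from baseline to each time point between the groups will be compared". The tests named are a two-sample t-test and a Mann–Whitney U-test. Table 3 repeats this for CMS, VAS, range of motion and SF-36 at weeks 4, 12, 18 and 24. Its footnote sends the analysis to Mann–Whitney "for data not conforming to normal distribution". No covariate appears in any analysis.

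Three other places bear on this:

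- Outcomes {12}, Table 1, gives the analysis metric as "Difference in the mean of change from baseline between the two groups" and makes weeks 4 and 12 the principal analyses of CMS.
- Sequence generation {16a}: "The randomization list will be stratified by study center". There are three hospitals.
- Sample size {14} works from a difference in means ("CMS increased by 24.32 (μ_r_) in the FSM group and increased by 10.31 (μ_c_) in the SM group"), and 15 patients per group are added because the trial is multicenter.

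**The concern.** These are methods the article states, so the point is not about detail left to an analysis plan. It has three parts of unequal weight.

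1. **The test is chosen from the data.** Mann–Whitney compares the ordering of two distributions. It does not test or estimate a difference in means, so on that branch the result matches neither the metric in Table 1 nor the mean difference and margin Δ behind the sample size. Each visit is tested separately, so the two principal time points could report different effect measures. With over 100 per group, comparing means does not require normal data, so the switch gains nothing.
2. **Baseline is not adjusted for.** A change score in effect fixes the regression slope on baseline at 1. Where the true slope is smaller, it over-corrects any chance imbalance and carries extra noise.
3. **Center is ignored after stratifying on it.** If centers differ, the unadjusted standard error is too wide and the test is conservative.

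At stake are precision and a fixed effect measure for the primary outcome.

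**Working it through.** **The plan's own figure.** Inputs from Sample size {14}: mean changes 24.32 and 10.31, so the difference is 14.01; "the standard deviation of the FSM group was 17.84", read here as the SD of change and used for both arms; Δ = 17.84/3 = 5.95; one-sided α 0.025; power 90%; ratio 1:1.

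n = 2 × 17.84² × (1.96 + 1.282)² / (14.01 − 5.947)² = 102.9, so 103 per group. The noncentral-t version gives 104, the stated number. The sample size therefore reproduces as an unadjusted comparison of means. With 140 per group and 20% dropout, 140 × 0.8 = 112 complete.

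**Baseline adjustment.** Let σ be the SD at each visit, assumed equal, and ρ the baseline–follow-up correlation. The documents do not give ρ, so a range is assumed.

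- Variance of the change score: 2σ²(1 − ρ)
- Residual variance under ANCOVA: σ²(1 − ρ²)
- Ratio: (1 + ρ)/2

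| ρ (assumed) | Variance ratio | n per group, 90% power | Power at 104 | SE at 104 (CMS points) | 112 count like |
|---|---|---|---|---|---|
| planned test | 1 | 103 | 90.3% | 2.47 | 112 |
| 0.3 | 0.65 | 67 | 98.1% | 1.99 | 172 |
| 0.5 | 0.75 | 78 | 96.4% | 2.14 | 149 |
| 0.7 | 0.85 | 88 | 94.2% | 2.28 | 132 |
| 0.8 | 0.90 | 93 | 93.0% | 2.35 | 124 |

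The n and power columns use the protocol's effect, margin and α, with the planned SD multiplied by the square root of the ratio. The last column is 112 divided by the ratio.

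On imbalance: with equal SDs the true slope is ρ, so a chance baseline difference of 1 point shifts the change-score estimate by 1 − ρ in the opposite direction. That is 0.7, 0.5 and 0.3 points at ρ = 0.3, 0.5 and 0.7.

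If the SDs differ, with baseline SD equal to k times follow-up SD, the ratio is (1 − ρ²)/(1 + k² − 2kρ). At k = 0.7 this is 0.91/1.07 = 0.85, 0.75/0.79 = 0.95 and 0.51/0.51 = 1.00 for the same three correlations, so the gain shrinks or vanishes. In large samples ANCOVA is never less precise than the change score.

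**Center.** Suppose 2%, 5% or 10% of the variance lies between centers (assumed). The unadjusted SE is then too large by the factor 1/√(1 − share). The true two-sided α is 2[1 − Φ(1.96/√(1 − share))] = 0.048, 0.044 or 0.039. Power at 104 per group is 90.5%, 90.9% or 91.5% unadjusted, against 90.9%, 91.7% or 93.0% adjusted.

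**Normality switch.** Simulation with 112 per arm, SD 17.84 and 4,000 runs. The article names no normality check, so Shapiro–Wilk at 0.05 in each arm is assumed. True mean change is equal in both arms throughout.

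| Shapes of the two arms | Switched to Mann–Whitney | t-test rejects | Switching rule rejects |
|---|---|---|---|
| both normal | 10.7% | 4.6% | 4.6% |
| mild skew (gamma, shape 8) vs normal | 77.7% | 5.0% | 7.0% |
| strong skew (gamma, shape 2) vs normal | 100% | 5.2% | 12.7% |
| opposite strong skew (extreme) | 100% | 4.9% | 40.2% |

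When shapes differ, the switching rule rejects more often than 5% although the mean changes are equal, because the rank test is answering another question.

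**The case against.** The planned t-test is not wrong. In a 1:1 randomized trial it is unbiased, holds its type I error and targets exactly the metric in Table 1. On the protocol's figures, 104 per group already gives 90.3% power against the margin and over 99.9% against zero, so the lost precision does not endanger the conclusion. All of this stands.

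The size of the baseline gain rests on a correlation that the documents do not give and on equal SDs. At ρ = 0.9 the 112 completers would count like only about 118 (112/0.95). The center effect is about 0.4 to 1.5 percentage points of power and errs on the conservative side. That stands too.

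If treatment has no effect at all, both arms share one distribution and the switch does little harm to type I error. The inflated rates arise only when means agree but shapes differ. This is fair, and it limits how far those rates can be read as error rates of the trial. It does not touch the mismatch between Table 1 and the Table 3 footnote.

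Δ appears only in the sample size; section {20a} plans no comparison with it under either test. The lack of an estimate to set against Δ is thus a property of the Mann–Whitney branch, while the missing comparison itself is a separate matter. Finally, section {20b} rules out additional analyses on the ground that there are no subgroups, so it is weak evidence that covariate adjustment was considered and rejected. The case here rests on {20a} and Table 3.

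**Conclusion.** The concern holds and should be acted on, though it does not invalidate the trial. The firmest part needs no assumption: the Table 3 footnote allows a test that does not address the difference in mean change defined in Table 1, and the choice can vary from visit to visit. The loss from not adjusting for baseline is certain in direction and uncertain in size: 35%, 25% and 15% of the variance at assumed correlations of 0.3, 0.5 and 0.7 with equal SDs, falling to 10% at 0.8 and possibly to nothing with a smaller baseline SD. The center part is minor. Confidence is high on the direction and moderate on the size.

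**What to change.** In section {20a} and Table 3, replace the two tests with one prespecified model for each continuous outcome: ANCOVA at each visit, or a mixed model over visits, with treatment, baseline value and center. Report the adjusted mean difference with its 95% CI at every visit, whatever the distribution looks like. Delete the normality footnote. If a rank analysis is wanted, keep a center-stratified one (van Elteren) as a sensitivity analysis only.

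The change should be dated before any grouped data are released for analysis. It costs analysis wording only: baseline values and center are already recorded, the planned SPSS V26 fits these linear and mixed models, and no patients, visits or measurements are added.

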## Methods: participants, interventions, and outcomes

### Study setting {9}

A total of 280 individuals with RCRSP will be recruited from three hospitals in China: (1) Shanghai Municipal Hospital of TCM, (2) LongHua Hospital Affiliated to Shanghai University of TCM, and (3) Shanghai GuangHua Hospital of Integrated TCM and Western Medicine. These three hospitals are grade III, class A, teaching hospitals affiliated to Shanghai University of TCM, and they are all located in the center of Shanghai, with convenient transportation, good medical conditions, and plentiful patient resources. These conditions will be conducive to the smooth development of the study.

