### Intervention description {11a}

Participants will receive FSM or SM in 4 therapy sessions once a week. Both groups will also receive the parallel daily home-based exercise program for 12 weeks.

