### Five-step shoulder manipulation

Massage. The therapist stands behind the patient and kneads the sternoclavicular joint on the affected site with the index and middle fingers. The intensity is determined by the patient’s acid reflux sensation, and the pressure continued for 30 s.Abduction. The therapist stands on the shoulder side of patient, assists the patient in abducting the affected shoulder to 90°, and applies appropriate upward and downward forces to allow the patient to engage in static confrontation with the relevant muscle groups resisting contraction for 30 s each time.Release. The therapist stands behind the patient’s shoulder with one hand stabilizing the acromioclavicular joint, and the other hand hooking four fingers into the lower third of the medial edge of the scapula. The therapist passively abducts and adducts the scapula with both hands, reciprocates for 4–5 times.Impact. The therapist stands behind the patient with the elbow flexed approximately 135° and the shoulder slightly prone and then holds the elbow in both hands and repeats transverse movements at an appropriate frequency to relax the shoulder. After complete shoulder relaxation, the therapist quickly lifts the humerus to the glenoid cavity to complete the internal impact of the glenohumeral joint.Shake. The therapist stands on the side of the patient, crosses the right wrist with the patient’s forearm on the affected side, and then shakes the shoulder joint clockwise 3 times and then counterclockwise 3 times.

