#### Implementation {16c}

The randomization list will be generated by Shanghai Medical Clinical Research Center and submitted to the randomization manager for storage. Upon participant enrollment, the therapist will obtain the randomization number and treatment regimen for the patient via phone or WeChat, which will not be known by the patients and outcome assessors.

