### Methods for additional analyses (e.g., subgroup analyses) {20b}

N/A. In this study, there are just two groups including FSM group and SM group, with no subgroups set up within the two groups. As a result, there is no additional analysis.

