In clinical trials, a placebo as a control treatment not only effectively evaluates the effectiveness of the treatment tested but also facilitates the implementation of blinding and eliminates several potential biases, such as patients’ dependence on therapists and expectations of treatment efficacy [27–29]. In manipulative studies, it is impossible to blind the therapist; therefore, using an inert manipulative therapy as a placebo to blind the participants is the best alternative. Previous studies have demonstrated the reliability of using SM as a placebo in manipulative studies [15, 30]. In this study, the inert treatment effect is achieved by applying no thrust and strictly confining the manipulation to the skin surface in accordance with the procedure tailored to FSM. In this study, the participants will be treated individually at different times to avoid communication and interference between participants. We hope to minimize potential differences by implementing the above interventions.

The main symptoms of RCRSP are pain, dysfunction, and loss of strength, and therefore a comprehensive evaluation tool is appropriate for the primary outcome. The evaluation content of the CMS basically covers all the symptoms of RCRSP and the adverse effects on quality of life, with good validity and responsiveness. Because the CMS is used widely in the assessment of shoulder diseases [31], we chose this measurement tool as the primary outcome of the study. Additionally, we will use VAS scores, ROM, and SF-36 scores to accurately quantify pain, function, and quality of life, respectively.

To provide a more accurate assessment, we intend to conduct this well-designed RCT to investigate both the efficacy and safety of RCRSP, contributing to worthy clinical evidence for manipulative therapy in RCRSP.

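### The planned tests use neither center nor treating therapist for a hands-on treatment. Depending on how therapists are deployed, the standard error is slightly too large or materially too small.

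*Protocol article*

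**What the plan says.** The protocol article (Statistical methods {20a} and Table 3) compares mean change in every outcome "from baseline to each time point between the groups will be compared using two independent samples" t-tests, or the Mann–Whitney U-test if the data are not normal. Neither center nor therapist enters.

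The relevant design facts are:

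- Study setting {9}: "A total of 280 individuals with RCRSP will be recruited from three hospitals in China". The number of therapists is not given.
- Sequence generation {16a}: "The randomization list will be stratified by study center". No other stratification factor is named.
- Intervention description {11a}: "Participants will receive FSM or SM in 4 therapy sessions once a week".
- Five-step shoulder manipulation: parts of the technique rest on the therapist's judgement. In the fourth step, for example, the therapist "repeats transverse movements at an appropriate frequency to relax the shoulder".
- Implementation {16c}: at enrolment "the therapist will obtain the randomization number and treatment regimen for the patient via phone or WeChat".
- Discussion: "it is impossible to blind the therapist".
- Sample size {14}: the formula treats patients as independent. It adds 15 per arm for the multicenter design, with no ICC or derivation.

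**The concern.** Patients treated by the same pair of hands may share part of their outcome. This is a separate source of dependence from center, because therapists within one hospital can differ both in general level and in how much more they achieve with FSM than with SM. An independent-samples test assumes no such sharing.

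The consequence depends on deployment, which the article does not state. If therapists are shared across arms, a difference in general level cancels from the comparison but stays in the estimated variance, so the test loses a little power. Ignoring center in a center-stratified trial acts in the same direction. If the FSM advantage differs between therapists, or the arms have different therapists, the opposite happens. The p-value then overstates the evidence that FSM would work in other hands, and a positive result could partly reflect particular practitioners.

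This is a stated choice of method, not a detail left for later. {20a} and Table 3 name the tests, and neither test can carry a center or therapist term.

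**Working it through.** **The plan's own figure.** The inputs in Sample size {14} are mean changes of 24.32 and 10.31, SD 17.84, Δ = 17.84/3 = 5.947, one-sided α 0.025 and power 0.90.

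n = 2 × (1.96 + 1.282)² × 17.84² / (14.01 − 5.947)² = 102.9, so 103. The stated 104 is reproduced within rounding (Δ rounded to 6.0 gives 104.3). The formula has no design effect.

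**Assumptions for the check.**

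- 112 evaluable per arm (140 × 0.80, the plan's dropout rate).
- T = 3, 6 or 9 therapists, in total if shared by both arms and per arm if not.
- ICC 0.01, 0.02 or 0.05.
- Equal caseloads, and one therapist per patient.

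T, the ICC and the caseload structure are assumed; the article gives none of them.

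**Case A: shared therapists who differ only in general level, caseloads balanced across arms.** The true variance of the difference is (1 − ICC) times what the t-test estimates. True error = 2[1 − Φ(1.96/√(1 − ICC))], which is 4.9% at ICC 0.01, 4.4% at 0.05 and 3.9% at 0.10. Simulation (20,000 trials per cell) gave 4.5% to 5.2% for ICC 0.01 to 0.05. With chance imbalance of therapists across arms the loss is smaller still.

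**Case B: the therapist effect is independent in each arm** (the treatment effect varies by therapist, or the arms have different therapists). With m = 112/T, the design effect is DE = 1 + (m − 1) × ICC, and true error = 2[1 − Φ(1.96/√DE)].

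| T | m | DE at ICC 0.01 / 0.02 / 0.05 | True error of the nominal 5% test |
|---|---|---|---|
| 3 | 37.3 | 1.36 / 1.73 / 2.82 | 9.3% / 13.6% / 24.3% |
| 6 | 18.7 | 1.18 / 1.35 / 1.88 | 7.1% / 9.2% / 15.3% |
| 9 | 12.4 | 1.11 / 1.23 / 1.57 | 6.3% / 7.7% / 11.8% |

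Simulated t-tests agree: 24.5%, 15.2% and 12.0% at ICC 0.05 for T = 3, 6 and 9.

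**Which remedy works in Case B?** Simulated at ICC 0.05 with therapists shared by both arms:

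| Analysis | T = 3 | T = 6 | T = 9 |
|---|---|---|---|
| Planned t-test | 24.5% | 15.2% | 12.0% |
| Linear model, therapist main effect | 24.9% | 15.7% | 12.4% |
| t-test on therapist-level FSM-minus-SM differences (T − 1 df) | 4.9% | 5.0% | 5.0% |

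The main-effect model does not help here. If therapists were nested in arms, a fixed therapist term would be collinear with arm.

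**Price of valid inference in Case B.** The interval widens by √DE × t(0.975; df)/1.971, where 1.971 is the t-quantile of the planned test. For T = 3, ICC 0.05 and shared therapists (T − 1 = 2 df), this is 1.678 × 4.303/1.971 = 3.7. For T = 6 and 9 it is 1.8 and 1.5. If therapists are nested (2T − 2 df), the factors are 2.4, 1.6 and 1.35.

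**The multicenter allowance.** 140/125 = 1.12, close to the DE of 1.11 for T = 9 and ICC 0.01. It adds patients but leaves the standard error formula unchanged.

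**The case against.** The strongest reply is that the article points to the milder case. Individual patients are randomized within center and the therapist is told each patient's regimen, which fits therapists who treat both arms. Harm then requires the FSM advantage to differ between therapists, and nothing in the article shows how much it does. This stands, and it is why the direction is left open. The article suggests shared therapists but does not state it.

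Case B also gives the sham arm as much therapist variation as FSM, although SM is scripted as surface contact without thrust. If only the FSM arm varies, the design effect becomes (DE + 1)/2. The error at ICC 0.05 is then 15.6%, 10.3% and 8.4% for T = 3, 6 and 9: smaller, but not removed.

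Delivery is partly standardized. Hold times, abduction angle and repetition counts are set, the DSMC checks technique every 2 weeks, and the research group inspects monthly. This may keep the ICC low. It does not make the tests use therapist or center.

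The number of therapists, their training and the CRF fields may well be in the full protocol, so their absence from the article is no fault in itself. The test, however, is fixed here.

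Three stronger readings are tempting and not supported:

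- That only a few therapists take part. No count is given. Treating 280 patients at three hospitals makes many patients per therapist likely, but no more than that.
- That {20b} rules out any therapist analysis. Its sentence "As a result, there is no additional analysis" follows from having no subgroups and does not address therapists.
- That adding a therapist term to the model cures the inflated error. The simulation shows that it does not.

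**Conclusion.** The point holds in this form: the fixed tests ignore the stratification factor and the treating therapist, and a better model is available at little cost. The size of the harm cannot be settled from the article. With shared therapists who differ only in level, true error is about 4% to 5%, a minor loss of power. With a treatment effect that varies by therapist, or different therapists in each arm, it is about 6% to 25% for 3 to 9 therapists and an ICC of 0.01 to 0.05. That inflation applies to conclusions beyond the participating therapists.

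A reader might infer that the trial's p-values will be too small, or that a positive result would belong to one or two skilled therapists. The article supports neither, because it gives no ICC and no therapist count and leans towards the crossed arrangement. If the 4-week pilot difference of 14.01 points recurred, the primary result would probably stay significant. The exposure is greater for smaller differences, later time points and secondary outcomes, which use the same test.

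**What to change.** 1. Record the treating therapist at each session, if the CRF does not already do so. State how many therapists there are, and that each treats both arms.
2. Replace the independent-samples tests with a linear model containing arm, center and therapist within center. This respects the stratification and removes the slight conservatism of Case A. It does nothing for Case B and should not be described as if it did.
3. Prespecify a sensitivity analysis in which the treatment effect may vary by therapist: either a random therapist-by-arm term, or a test on therapist-level FSM-minus-SM differences with therapist-level degrees of freedom. Report the therapist-specific effects.
4. If therapists prove to be few, limit the conclusion to the participating therapists.

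Cost: one data field and revised analysis wording, with no extra patients. The real downside is the sensitivity interval. With few therapists it will be clearly wider than the planned one: at ICC 0.05 with shared therapists, about 1.5 times as wide with nine and 3.7 times with three. Its role should therefore be set in advance.
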